### RNA sequencing

2.9.

AEFIs may be caused by overactive or inappropriate immune responses targeting self-antigens, adverse reactions to viral protein expression, or other dysregulated physiologic responses. These responses must begin with transcriptional changes in the reactive cells and/or tissues. Gene expression analysis of PBMCs will be used to evaluate whether there are transcriptomic signatures associated with AEs following COVID-19 vaccination that can be detected in the peripheral blood. In the case of VITT/TTS, the primary pathology is blood-based and therefore PBMC transcriptomic data will complement the additional analysis of the proteome and metabolome in blood, providing a fuller picture of the molecular mechanisms underlying this adverse event.

PBMC samples will be thawed and cultured under appropriate conditions (e.g., unstimulated or antigen-stimulated) at the Mayo Clinic Vaccine Research Group (MVRG)[ [67]. RNA will be extracted using Qiagen kits and sequencing libraries will be prepared using the TruSeq Stranded mRNA Library Prep kit. mRNA-Seq will be performed in the Mayo Clinic Medical Genome Facility using the Illumina NovaSeq 6000 platform. Flow cell samples will be sequenced as 51 × 2 paired-end reads using HCS v2.0.12 data-collection software or an equivalent platform. Base-calling will be performed using Illumina’s RTA version 1.17.21.3. Gene sequencing data will be aligned using the MAP-RSeq V1 pipeline to the h19 human genome.

### Immunophenotyping using mass cytometry time of flight

2.10.

Immunopathology can be mediated by inappropriate antigen stimulation of lymphocyte populations (e.g., self-reactive T cells) or activation of innate immune cells (e.g., mast cells or basophils triggering anaphylaxis) [68]. Immunophenotyping panels provide an opportunity to comprehensively evaluate both activation status and expansion/contraction of critical immune cell populations that may be responsible for vaccine-related SAEs [69]. CyTOF will be performed with the use of mass cytometry through Mayo Clinic’s Immune Monitoring Core. The Core has a validated panel consisting of 36 antibody markers covering a broad range of leukocyte populations (supplementary file 2) [70].

### Genomics analyses

2.11.

#### Genome-wide association studies (GWAS)

2.11.1.

Extracted DNA from saliva samples will be genotyped with a custom Illumina Global Screening Array (GSA version 3.0 with additional pharmacogenomic content) including genetic variation throughout the genome (500,000 genome-wide markers), further enriched with pharmacogenomic variants including >45,000 variants in core drug absorption, distribution, metabolism, and elimination genes, and > 24,000 variants in major histocompatibility complex (MHC)/HLA gene regions. The array captures both common and rare variants collected from large-scale sequencing projects.

Previously reported candidate genes potentially related to the pathogenesis or biological mechanisms of GBS, TTS/VITT, myocarditis, and pericarditis will be also genotyped by either the custom GSA array or by custom TaqMan genotyping assays. Candidate genes for GBS include, but are not limited to, HLA alleles, IL-10, KIR, TNF-α, CD1, and FcγR. Candidate genes for TTS/VITT include, but are not limited to, F5, F2, PROC, and PROS1. Candidate genes for myocarditis and pericarditis include, but are not limited to, BAG3, DSP, PKP2, RYR2, SCN5A, and TNNI [71,72].

Genotyping will be followed by whole genome imputation of common variants using SHAPEIT (v2) and IMPUTE2 (v2.3.2) in combination with the Phase 31,000 Genomes Project reference panel and imputation of classical HLA alleles and HLA-region variants using SNP2HLA (v1.0.2) in combination with Type 1 Diabetes Genetics Consortium (T1DGC) reference panel. This will yield a final genotyped and imputed dataset of ~10 million variants per sample.

#### Exome sequencing

2.11.2.

From each of the three case groups, 50 of each the most severe AE patients who are categorized as Brighton Collaboration Level One cases of COVID-19-induced GBS, TTS/VITT, or myocarditis/pericarditis will also be selected (a total is 150 for three AEs) to perform exome analyses. This will complement genome-wide genotyping, particularly in protein-coding regions, to identify the most possible disease-causing mutations. The public exome sequencing database, gnomAD, as reference controls will be used to investigate novel and rare genetic variants related to these three specific AEs. Following library preparation with an IDT Capture Expanded Exome Kit, exome sequencing to a mean coverage of 100× will be performed using paired end sequencing (2 × 150 bp) on an Illumina Sequencing platform (NovaSeq platforms). The sequence data will be processed according to GATK Best Practices (v4), using BWA-MEM for alignment of reads to the GRCh38 reference genome on the local high-performance computing cluster. Significant variants identified from the GWAS discoveries will be further validated by genotyping (e.g., TaqMan assays) or sequencing.

### Epigenetics

2.12.

Gene expression is controlled, in part, by epigenetic regulatory features such as DNA methylation. The aim of these experiments is to perform an unbiased measurement of DNA methylation patterns across CpG sites across the genome. DNA methylation patterns that do correlate with vaccine SAEs may provide insights into the biological activities that are dysregulated and contribute to those AEs. Following DNA extraction from PBMC samples, genome-wide methylation patterns will be assessed using either an Illumina Methylation BeadChip or RBBS followed by methyl-Seq.

### Human in vitro modeling

2.13.

To assess whether vaccine-induced molecular signatures may predict AEFIs, where facilities exist, we will collect study participant blood to generate cryopreserved PBMCs and matched autologous plasma. These will be batch shipped to the Precision Vaccines Program (Boston Children’s Hospital, Boston, MA) to conduct human in vitro assays such as PBMCs cultured in 10 % autologous plasma and tissue construct assays as previously described [73-75]. Conditions tested will include vehicle control, agonists of pattern recognition receptors (PRRs) involved in COVID-19 vaccine-induced innate immune responses [76], and authorized/approved COVID-19 vaccines at three dilutions: 1:1000, 1:100 and 1:10 vol/vol. Cellular and soluble fractions will be collected and cryopreserved for downstream systems biology as we have described [77]. Resulting cellular and molecular signatures will be integrated with clinical and immunologic data to provide insights into modeling human in vitro vaccine responses in relation to AEFIs, an approach supported by the United States Food and Drug Administration (FDA) Modernization Act 2.0 [78] aimed at identifying actionable biomarkers to inform future vaccine discovery and development. This human in vitro modeling system provides an ability to recapitulate key aspects of tissue-specific immune responses [70,75,79,80] adding important mechanistic insight to complement in vivo analyses.

## Data management and analytical strategy

3.

### Study oversight and reporting

3.1.

Data are submitted to a central REDCap database hosted and maintained by the Data Management and Analysis Core (DMAC) (PVP, Boston Children’s Hospital; Boston, MA, USA). Participant data will be transferred to the INSIS REDCap database from participating INSIS networks and partners using secure transfer protocols. INSIS sites will be responsible for local quality control and retain ownership of their data. The DMAC will conduct additional data quality checks on the database and maintain a centralized data repository and analytic platform.

Standard forms and labels will be used for sample tracking and linkage to clinical databases. Patient samples will be linked to their record in the database by a unique study ID. The sample management system LDMS [41] will be used to track samples from the point of collection to the analytic laboratories by scanning a sample-specific barcode, which carries a unique sample identifier (sample ID). Date of sample collection, sample type, and volume at each timepoint will be recorded on a sample processing form (SPF) and these metadata will be captured electronically by the central INSIS database. The DMAC will oversee sample tracking and shipping.

Within the framework of executed material transfer and data transfer use agreements (MTAs and DTUAs), and appropriate institutional approvals, INSIS sites will partner with the PVP, Mayo Vaccine Research Group MVRG, Ospedale Pediatrico Bambino Gésu (OPBG), and other INSIS affiliated laboratories to coordinate sample shipping for the multi-omics analysis described above. Integration of clinical and biological data will be conducted using a cloud-based bioinformatic analytic infrastructure. INSIS will work with GVDN to coordinate transfer of clinical data and DNA samples collected at INSIS sites to GVDN (Canadian Pharmacogenomics Network for Drug Safety (CPNDS) lab at University of British Columbia) for processing and analysis.

### Data harmonization framework

3.2.

Harmonized procedural and data processing pipelines across assays are coordinated via the INSIS Data Management Working Group (DMWG) with support from the DMAC. As the cohort is recruited, plans will address missing clinical data and samples and appropriately randomize samples for each assay type to eliminate selection bias and evenly distribute confounding variables. Power calculations will be conducted to ensure that the study is adequately powered to detect significant differences or associations in the data, accounting for potential variability and expected effect sizes. Standardized metadata templates and controlled vocabularies will be applied to ensure data interoperability across sites and assay platforms. As part of our quality control and assurance measures, we recognize that self-reported demographic variables such as gender and race may vary in consistency across study sites. We will incorporate both self-reported and where available, biologically inferred variables (e.g. genetic ancestry, sex chromosome-linked gene expression) during analysis.

Once the data are uploaded to the INSIS study database, DMAC data managers and biostatisticians will coordinate and verify quality control (QC) processes for data collected/generated at clinical sites and Core Labs. They will also perform additional quality assurance (QA) to maintain the highest possible accuracy of clinical, immunologic, and systems biology data before reporting and analysis in the centralized cloud computing system (Fig. 4).

### Centralized computational platform and data deposition

3.3.

A cloud computing platform specifically for the INSIS study will be utilized for encrypted, access-controlled data storage and analysis resources [81]. This will include a data and analysis dashboard that allows INSIS investigators to upload, store and analyze both raw and processed computable data within a centralized computing environment. The computing platform will offer a secure environment for developing, testing, and running scripts, as well as performing quality control (QC) and quality assurance (QA) on data generated by the Core Labs. This centralized system will ensure that the INSIS Core Labs adhere to shared data standards and maintain internal consistency, facilitating accurate and integrated data analysis. This setup will be designed to facilitate data sharing and downstream analyses by INSIS investigators and the broader research community, who will be able to access the data and associated metadata via a public data repository such as dbGAP [82] or ImmPort [83] (immport.niaid.nih.gov). Deidentified quality assured published data will be deposited to public repositories according to the funder’s policies.

### Analysis of clinical features and outcomes

3.4.

Clinical features, results of investigations, other exposures or risk factors, and outcomes of the AEFI will be compared within each subgroup by vaccine product, age, biological sex, self-reported gender, and race. Examples of analysis will include multivariable regression analysis which will identify demographic and clinical factors associated with Brighton Collaboration case definition-confirmed TTS/VITT, myocarditis, and pericarditis in cases versus healthy controls. Additionally, we plan to compare factors related to post-vaccination versus non-vaccine associated myocarditis and TTS/VITT versus HIT/VITT-like non-vaccine associated syndromes. Similar approaches will be employed for new AEFIs that emerge as safety signals.

With sufficient sample size, some samples may be used for discovery cohorts and others for replication, with one network (e.g., INSIS) leading an omics discovery analysis and providing samples for the replication of another network’s analyses. Similar sample size and matching approaches will be used for new AEFI targets. INSIS will partner with GVDN to recruit cases and controls for genomics analysis in GVDN-led studies.

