VITT has been linked to adenoviral vector COVID-19 vaccines (e.g., ChAdOx1 and Ad.26.COV-2.S). First reported in March 2021, VITT is characterized by rapidly progressive thrombosis, particularly in cerebral venous sinuses and splanchnic circulation veins, accompanied by thrombocytopenia and markedly elevated D-dimer and anti-platelet factor 4 (PF4) antibodies driving platelet activation [11-15]. The incidence of VITT ranges from 0.1 to 1.2 cases per 100,000 vaccinations following Ad26.COV-2.S and 1 to 5 per 100,000 following the first dose of ChAdOx1 vaccine [16]. Early diagnosis and treatment have reduced case fatality rates from as high as 40 % to 13–15 % [17].

Myocarditis and pericarditis emerged as safety signals following the rollout of COVID-19 mRNA vaccines. Although these vaccines have been pivotal in controlling the pandemic, there is an increased incidence of myocarditis and pericarditis, particularly among young males aged 12–29 years after the second dose [18,19-25]. Initial data suggested most patients appeared to recover quickly. Ongoing studies are focused on determining long-term outcomes, including resolution of cardiac MRI changes and cardiac-specific biomarkers, with some studies reporting persistence of MRI changes and symptoms in a subset of patients [26]. Importantly, despite these rare events, the benefits of COVID-19 vaccination in preventing severe disease, hospitalization, and death continue to far outweigh the risks. The mRNA platform is now being used to develop vaccines against a range of other diseases including influenza, Respiratory Syncytial Virus (RSV), Nipah, and Lassa fever, as well as for non-infectious indications such as cancer [11,27].

Myocarditis and pericarditis have also been reported following non-mRNA COVID-19 vaccines, including the adjuvanted protein subunit vaccine Novavax NVX-CoV2373 and AstraZeneca’s ChAdOx1 [23]. Early studies suggest that the spike protein may contribute to these rare cardiac events [28,29]. Ongoing research into the underlying biological mechanisms is essential to refine our understanding of vaccine safety. Continued surveillance and investigation are critical to ensuring public confidence and the safety of vaccination programs.

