#### Case-control matching

2.4.3.

Cases will be matched to healthy controls, recruited through observational vaccine studies and other approaches, who received the same vaccine platform and, where feasible, the same product (e.g., BNT162b2 or mRNA-1273) and did not develop an AEFI. Samples from these controls will be matched to cases at a ratio of at least 1:1 and ideally 3:1 for multi-omics analysis by age group, biological sex, vaccine type, and ancestry.

Cases may also be frequency matched to controls with a non-vaccine-associated TTS/VITT-like condition (e.g., heparin-induced thrombocytopenia [HIT]) or non-vaccine-associated myocarditis or pericarditis, who meet Brighton criteria and have samples collected and stored at the time of their clinical presentation. Matching will be done by age (±5 years), biological sex, ancestry (where possible), and vaccine received (for healthy controls).

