#### Sample collection and processing

2.4.4.

Both cases and controls will undergo data and sample collection for multi-omics analyses, including transcriptomics, proteomics, and metabolomics using a standardized protocol. Samples will be captured as close to the onset of an AE as possible, up to 12 weeks after the event, with follow-up samples collected as needed. Participants will also be invited to consent to saliva or blood sampling for DNA extraction and genotyping under the GVDN genomics protocol.

Sample collection for cases and controls will be conducted using retrospective residual clinical samples or prospectively at selected sites. At each timepoint (see Table 1), peripheral blood (5–15 ml) will be collected according to protocol. Where processing facilities are available, whole blood (20–30 ml) will be collected for PBMC isolation. Additional sample types, including serum, may be collected according to site-specific or study-specific protocols (refer to INSIS Study SOP in supplementary file 1). Samples for multi-omics analysis will be stored at the participating site until they are ready to be shipped on dry ice or liquid nitrogen to an INSIS laboratory with biobanking facilities, such as the Precision Vaccines Program (PVP), where they will be stored at −80 °C until analysis (Fig. 2). As of May 15, 2025, 7 sites have entered data for 154 cases and 110 controls into the INSIS REDCap database, with >1100 samples (including serum, plasma, PBMC, and saliva) recorded in the INSIS REDCap database. Additionally, > 1600 sample aliquots have been entered into the Laboratory Data Management System (LDMS) [41] sample management system. These numbers will continue to increase as sites enter their data into the INSIS REDCap and LDMS databases.

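### The regression meant to identify demographic risk factors compares cases with healthy controls matched on age, sex and vaccine platform, so it cannot estimate those effects

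*Protocol article*

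**What the plan says.** Section 3.4 (Analysis of clinical features and outcomes) gives as an example of the planned analyses a "multivariable regression analysis which will identify demographic and clinical factors associated with Brighton Collaboration case definition-confirmed TTS/VITT", and continues to "myocarditis, and pericarditis in cases versus healthy controls". The aim thus covers demographic as well as clinical factors, and the comparator is the healthy controls.

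Section 2.4.3 (Case-control matching) describes how those controls are obtained: "Cases will be matched to healthy controls, recruited through observational vaccine studies and other approaches, who received the same vaccine platform", with the same product where feasible. Samples from them are "matched to cases at a ratio of at least 1:1 and ideally 3:1", "for multi-omics analysis by age group, biological sex, vaccine type, and ancestry". The section closes with a second statement of the matching rule: "Matching will be done by age (±5 years), biological sex, ancestry (where possible), and vaccine received (for healthy controls".

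The Introduction reports that the excess of myocarditis and pericarditis after mRNA vaccines is seen "particularly among young males aged 12–29 years after the second dose". Section 3.4 does not remove the matching variables from the factors to be identified.

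**The concern.** Matching gives controls the same distribution of the matched factor as the cases. A comparison of the two groups then carries no information on whether that factor raises risk. Age and biological sex are leading demographic variables in this study, and both are matching variables. A stated aim of the regression therefore cannot be met with the controls that the article describes.

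The risk is one of interpretation. If coefficients for sex or age from this model were reported, they would lie near the null whatever the truth. They could be read as evidence against the age and sex gradient that the Introduction reports and that motivates the hormone work in Section 2.6. Section 3.4 extends similar analysis and matching approaches to new adverse events, so the problem would carry over.

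**Working it through.** **Inputs from the article.** Comparator: healthy controls (Section 3.4). Matching factors and ratio: Section 2.4.3. Number of cases for illustration: 154, from Section 2.4.4 ("7 sites have entered data for 154 cases and 110 controls into the INSIS REDCap database"). That is 110/154 = 0.71 controls per case to date, with control types not separated and accrual continuing, so only the 154 is used. The article gives no effect size or power for this regression (Section 3.2 defers power calculations), so there is no stated figure to reproduce.

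**Assumptions.** Source population half male, ages uniform from 12 to 70. True odds ratio (OR) for male sex 4, and also 2. True OR per 10 years of age exp(10 × −0.04) = exp(−0.4) = 0.67. One binary clinical factor, not matched, with true OR 2; in some settings it is commoner in males (log-odds higher by 0.8).

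**Step 1: sex, pooled comparison.** Let p be the proportion male among cases. With sex matching at a fixed ratio, the proportion male among controls is also p, so

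OR = [p/(1−p)] / [p/(1−p)] = 1 for any p.

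For a rare event with true OR 4, p = (0.5 × 4)/(0.5 × 4 + 0.5 × 1) = 0.80.
- Matched controls: (0.8/0.2)/(0.8/0.2) = 1.
- Unmatched controls: (0.8/0.2)/(0.5/0.5) = 4.

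**Step 2: sex, conditional analysis.** For a 1:1 pair the likelihood contribution is exp(βx₁)/[exp(βx₁) + exp(βx₀)], where x₁ is the case's value and x₀ the control's. Sex is the same in both, so this equals 1/2 for every β and the effect is not estimable. The same holds for platform. Age contributes only its variation inside the matching band.

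**Step 3: simulation.** 154 cases, with controls drawn either unmatched or individually matched on sex and age ±5 years. A logistic model on sex, age and the clinical factor was fitted, with 150 replicates per setting. ORs are from median estimates; the last two columns give the share of replicates with p < 0.05.

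| Controls | Controls per case | Clinical factor tied to sex | Sex OR | Age OR per 10 y | Clinical OR | Sex p<0.05 | Age p<0.05 |
|---|---|---|---|---|---|---|---|
| Unmatched | 1 | no | 4.169 | 0.657 | 2.076 | 100% | 100% |
| Unmatched | 1 | yes | 3.921 | 0.677 | 1.974 | 100% | 100% |
| Unmatched | 3 | no | 4.020 | 0.662 | 2.055 | 100% | 100% |
| Unmatched | 3 | yes | 3.910 | 0.677 | 1.930 | 100% | 100% |
| Matched | 1 | no | 1.006 | 0.990 | 2.006 | 0% | 0% |
| Matched | 1 | yes | 0.890 | 0.989 | 1.958 | 0% | 0% |
| Matched | 3 | no | 1.005 | 0.990 | 2.023 | 0% | 0% |
| Matched | 3 | yes | 0.882 | 0.989 | 2.007 | 0% | 0% |

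With a true sex OR of 2, one control per case and a clinical factor unrelated to sex, matched controls gave 0.999 (0% significant) and unmatched controls gave 1.972 (78% significant).

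The sex and age effects disappear under matching, and going from one to three controls per case does not bring them back. Where the clinical factor is tied to sex, the sex estimate even falls slightly below 1. The unmatched clinical factor is recovered throughout.

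**Step 4: ancestry and product.** Ancestry is matched where possible and product where feasible. Their coefficients mix a true effect with the success of matching, so they are distorted by an amount that cannot be stated in advance.

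**The case against.** The best defence is that matching may serve only the multi-omics samples. The ratio is stated "for multi-omics analysis by age group, biological sex, vaccine type, and ancestry", whereas Section 3.4 concerns clinical data, which Section 2.3 collects on all participants. A wider control set could therefore be meant. This does not settle the matter: the opening and closing matching statements in Section 2.4.3 carry no such limit, and no other healthy controls are described. If a wider set is intended, the article needs to name it.

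It can also be said that the regression is only an example, that the study's aim is pathophysiology, for which matching on age and sex is sensible, and that the age and sex gradient is taken as known. This limits the weight of the point. The multi-omics comparisons and the comparisons of features among cases by age, sex or product are not harmed. Some demographic items, such as country of enrolment, self-reported gender and race, are not named as matching variables, although gender and race are closely tied to sex and ancestry.

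Four stronger readings are tempting but not supported:
- *The plan specifies a model that ignores the matching.* It says only that the regression is multivariable. A conditional logistic model fits that description, and the choice may be left to an analysis plan.
- *Clinical factors are biased toward the null.* That would require leaving the matching factors out of the model. With sex and age included, the simulated clinical factor was recovered at 1.96 to 2.02 against a truth of 2.
- *Ratio matching and frequency matching contradict each other.* They refer to different groups: healthy vaccinated controls, and controls with non-vaccine-associated disease. Only the age rule (age group or ±5 years) needs to be made uniform.
- *All demographic and vaccine effects are forced to null.* This applies to sex, platform and most of age, but not to ancestry or product, which are matched only in part.

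**Conclusion.** The point holds in this limited form: Section 3.4 states an analysis aim that the controls described in Section 2.4.3 cannot deliver. Sex and platform effects, and age effects beyond the matching band, are not estimable from matched healthy controls under any model. Ancestry and product effects are distorted to the extent that matching succeeds. In the simulation a true sex OR of 4 or 2 came back as about 1, and an age OR of 0.67 per 10 years as 0.99.

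The effect sizes and source population are assumptions, but the collapse for sex follows from the algebra and does not depend on them. The conclusion does assume that the regression uses the matched healthy controls, the only healthy controls that the article describes. A reader might infer that the study will report no association with male sex or young age. The article does not say that it will report those coefficients as findings. The supported statement is that such a coefficient, if reported, would be an artefact.

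**What to change.** In Section 3.4, limit the regression of cases against matched healthy controls to factors not used for matching, and to effect modification by the matched factors. State that the matching is accounted for, either by conditioning on matched sets or by keeping the matching factors in the model as nuisance terms. State that coefficients for age, sex, ancestry or race, and vaccine from this comparison will not be interpreted. Describe those factors in cases only, or against an unmatched vaccinee or surveillance denominator where one is available. If an unmatched healthy-control set is in fact intended for the clinical regression, name it and its source.

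In Section 2.4.3, give one age-matching rule for healthy controls.

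The cost is a few sentences in two sections, with no change to recruitment or assays. The study gives up a claim about demographic risk factors that its matched sample could not have supported.

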### Clinical data collection

2.3.

All INSIS sites will transfer the raw data from their database to the INSIS REDCap database, which is designed to capture general common data elements for all participants including age, country of enrollment, biological sex, self-reported gender, COVID-19 vaccination details, relevant past medical history, relevant medications, and details of the AEFI/condition including interval from vaccination to symptom onset (if applicable), specific symptoms, and diagnostic results. Details of the AEFIs will be captured in forms derived from the Brighton Collaboration Case Definitions for TTS/VITT and myocarditis/pericarditis to ensure each case is evaluated using consistent criteria. At each follow-up visit, data will be collected on any changed signs or symptoms including those associated with myocarditis, pericarditis, or TTS/VITT to detect persistent or recurrent disease activity.

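### The risk-factor regression compares cases with *healthy* controls, and nothing in the article ensures that those controls were not selected on the medical history and medications that may be tested

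*Protocol article*

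**What the plan says.** Section 3.4 (Analysis of clinical features and outcomes) offers, as an example, a multivariable regression intended to "identify demographic and clinical factors associated with Brighton Collaboration case definition-confirmed TTS/VITT, myocarditis, and pericarditis in cases versus healthy controls". The same section says that "Clinical features, results of investigations, other exposures or risk factors, and outcomes of the AEFI will be compared within each subgroup".

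Section 2.4.3 (Case-control matching) describes the controls: "Cases will be matched to healthy controls, recruited through observational vaccine studies and other approaches, who received the same vaccine platform", with the same product where feasible, "and did not develop an AEFI". On how the samples are paired it reads: "matched to cases at a ratio of at least 1:1 and ideally 3:1 for multi-omics analysis by age group, biological sex, vaccine type, and ancestry". Prior health is not a matching variable.

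Section 2.3 (Clinical data collection) includes "relevant past medical history, relevant medications, and details of the AEFI/condition" among the data elements common to all participants.

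Section 2.1 (Study procedures) finds cases by other routes: referral, laboratory submissions and AEFI surveillance.

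**The concern.** The aim of the regression is to find what distinguishes vaccinees who develop the event from vaccinees who do not. The controls should therefore show how common each factor is among the vaccinees who gave rise to the cases, including those with chronic disease or on treatment. The article names *healthy* controls and recruits them by a different route from the cases.

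If that label, the eligibility rules of a source study, or the tendency of fitter people to volunteer kept some people with a condition out of the control group, then control selection depended on the exposure under test. The condition would look over-represented among cases even if it had no bearing on the event.

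The results are meant to inform risk-benefit assessment and personalised vaccination (Abstract, Introduction and Conclusions). A comorbidity or medication wrongly flagged as a risk factor could bear on advice to people who have it. Section 3.4 also carries similar approaches forward to new AEFIs, so the weakness would be inherited.

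**Working it through.** The article gives no effect size, power figure or health criterion for this comparison, so there is no stated figure to reproduce. The steps below show what selection of controls on an exposure would do.

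**Inputs**
- From the article: 154 cases and 110 controls entered by 15 May 2025 (section 2.4.4), not divided by AEFI or by type of control.
- Assumed: p, the prevalence of a condition or medication among the vaccinees who gave rise to the cases; k, the fraction of people with it who still qualify as controls (everyone without it qualifies); a true odds ratio of 1, so that prevalence in cases is also p; a two-sided 5% test.

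**Step 1: expected odds ratio**
- Control prevalence: p0 = pk / (pk + 1 − p).
- Control odds: p0/(1 − p0) = k × p/(1 − p).
- Odds ratio: [p/(1 − p)] / [k × p/(1 − p)] = 1/k, at any prevalence and any sample size.

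| k | Odds ratio for a factor with no effect |
|---|---|
| 1.00 | 1.00 |
| 0.75 | 1.33 |
| 0.50 | 2.00 |
| 0.25 | 4.00 |

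**Step 2: how often this would reach significance (illustration only)**

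Wald statistic: z = ln(1/k) / SE, with SE² = 1/[154 p(1 − p)] + 1/[110 p0(1 − p0)]. The chance of a false harmful finding is Φ(z − 1.96), against a nominal 2.5% in that direction.

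Worked case, p = 0.20 and k = 0.50:
- p0 = 0.10/0.90 = 0.111
- SE² = 0.0406 + 0.0920 = 0.1326, so SE = 0.364
- z = 0.693/0.364 = 1.90
- Φ(1.90 − 1.96) = 0.48

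| p | k = 0.75 | k = 0.50 | k = 0.25 |
|---|---|---|---|
| 5% | 7% | 16% | 33% |
| 10% | 9% | 28% | 57% |
| 20% | 14% | 48% | 87% |

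A different set-up, in which control prevalence is simply p(1 − s) for a screened-out share s, gives the same direction and similar odds ratios: 1.42, 2.25 and 4.75 at p = 20% and s = 25%, 50% and 75%.

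**Step 3: does anything in the article remove it?**
- *Matching on age group, sex, vaccine type and ancestry* (2.4.3): no. Within a matched stratum the controls would still be depleted of the exposure.
- *Covariate adjustment* (3.4): no. The coefficient of the exposure is itself the distorted quantity.
- *Randomising samples for each assay*, which section 3.2 links to selection bias: no. It governs the order of laboratory work, not who was recruited.
- *Comparison with non-vaccine-associated disease* (3.4): no. It answers a different question.

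**The case against.** The strongest reply is that the article contains no health screen. Beyond the word *healthy*, section 2.4.3 asks only for the same vaccine platform and no AEFI, which is close to the right comparator. In sections 2.4.1, 2.4.2, 2.4.3 and 3.5 the word is set against controls with non-vaccine-associated disease, so it may be only a label for the other control group. The source studies are described as observational, and other routes are allowed. This largely stands. A reader might infer that controls were chosen for being healthy and that comorbidities will therefore look like causes. The documents do not support that: no comorbidity or medication exclusion is written, and section 3.4 speaks of association, not cause.

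Three further points stand in part.
- **Covariates.** Section 3.4 says demographic and clinical factors and offers the regression as an example. That medical history and medication will enter the model is an inference from section 2.3, though a natural one.
- **Cases.** Section 2.1 has cases assessed to rule out other causes. For some conditions that could remove affected cases and pull the odds ratio down, so upward bias is a tendency, not a certainty for every factor.
- **Illustrative rates.** The counts are interim and pooled over AEFIs and control types, so the separate contrasts are smaller and, at the same k and p, would reach significance less often.

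Eligibility detail may also sit in the full protocol or the study SOP, neither of which is shown. What the objection does not remove is that, in section 2.4.3, vaccination and absence of an AEFI are added to *healthy* and do not define it. Read literally, section 3.4 names an unsuitable comparator for this aim, and nothing in the article guards against the consequence.

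**Conclusion.** The point holds conditionally. For the stated aim, the comparator should be vaccinees without the event regardless of prior health, and the article names healthy controls recruited separately from cases. If any health selection took place, by definition, source-study eligibility or volunteering, associations with medical history and medication would tend to be biased away from the null. The planned matching and adjustment would not correct it.

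The size is 1/k for a factor with no true effect. That rests on k, which the article does not give; at k = 1 there is no bias. The significance rates rest also on an assumed prevalence and on pooled interim counts. They show only that moderate selection could produce false findings, and they do not predict this study's error rate. The change is worth making because it alters which conclusions the regression can support.

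**What to change.** 1. In sections 2.4.3 and 3.4, state that controls for the risk-factor regression are vaccinees of the same platform without the index event, not selected on prior health or medication. If *healthy* means only free of an AEFI and of the comparison diseases, say so.
2. Record the eligibility criteria of the source study for each control.
3. Where a source excluded a condition or medication, leave its controls out of the model for that factor, or do not report or interpret that factor from this contrast.

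The cost is some protocol and analysis wording and one source-eligibility field per control, with no new study procedures. The downside is fewer controls, or no estimate at all, for some clinical factors.
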